#### Exclusion criteria

We will exclude patients with laboratory findings in the following ranges: aspartate transaminase (AST) ≥ 60 IU/L, alanine transaminase (ALT) ≥ 60 IU/L, and creatinine > 1.2 mg/dl. Participants will be ineligible if they have undergone Western medical treatment or traditional medical treatment or taken oral contraceptives/antibiotics for acne within 2 weeks prior to recruitment or are pregnant, lactating, or planning to become pregnant during the study. Participants will also be excluded if they are not willing to comply with this study protocol. During the 8 weeks after enrollment in this trial, no concomitant acne therapy will be permitted.

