### Secondary outcomes

Secondary outcomes will evaluate the mean percentage change of non-inflammatory lesions and the total of both inflammatory and non-inflammatory lesions, the differences in temperatures of the DITI points on the face, Visual Analogue Scale (VAS) [score 0 (no symptoms) to 100 (severe symptoms)], and the Investigator Global Assessment scale for Facial Acne Vulgaris (IGA; after evaluation from score 0 (clear) to 4 (severe)) [10] from baseline to the end of the trial (at 8 weeks) between CBT treatment and the placebo control groups. Serum cortisol and dehydroepiandrosterone-sulfate (DHEA-S) will be assessed using clinical laboratory tests at weeks 0 (baseline) and 8 (end of the trial).

VAS and IGA will be checked every session from baseline (just before randomization) through the 8 weeks after randomization. A Lumix DMC-LX2 digital camera (Panasonic, Osaka, Japan) will be used to photograph the front and both sides of each patients face, so that the inflammatory and non-inflammatory lesions can be counted independently at weeks 0 (baseline), 4 and 8 (end of the trial) by a clinical specialist who has been in clinical practice for more 5 years. We will consider black and white head comedones to be non-inflammatory lesions and the inflammatory papules, pustules and cysts to be inflammatory lesions.

Correlations between the inflammatory lesion count and the temperatures of the DITI points at baseline, 4 weeks, and 8 weeks, and the frequency of abnormal liver and kidney function during this trial will also be secondary outcomes. Additionally, we will analyze the correlation between the temperatures of the DITI points and the severity of the Korean Acne Grading System (KAGS) at baseline and the end of the trial (at 8 weeks). Finally, we will analyze the success rate of blinding between the actual treatment and the perceived treatment allocations.

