### Adverse events and safety monitoring

All unexpected adverse events related to CBT or the placebo intervention will be reported to the investigator by participants and written on the individual case report form by the investigator. Safety will be assessed by the reporting of clinical laboratory tests and adverse events. Clinical laboratory tests, including AST / ALT and creatinine, will be performed at screening and week 8 (the end of the trial). Each participant will be monitored for adverse events (pain at acne lesions or other sites, nausea/vomiting, fatigue, allergic reaction, and any adverse events related to intervention) after each visit.

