### Statistical methods

#### Statistical analysis plan

Statistical analyses will be conducted on both intension-to-treat (ITT) and per-protocol (PP) bases, with a 95 % confidence interval using SPSS version 12.0 for Windows. Based on the ITT population, the primary outcome and safety outcome will be tested. Secondary outcome will be analyzed on both the ITT and PP populations. The ITT analysis will consider all randomized participants with at least one measurable outcome value during the study. Missing values from drop-out participants will be imputed by the last observation carried forward (LOCF) method. Data will be displayed as the mean ± standard deviation (SD) for continuous data or n (%) for categorical data.

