### Baseline data and outcome data

An independent *T* test will be performed for comparison of the baseline values between the CBT and placebo groups. The independent *T* test will be used to examine the mean percentage change of the inflammatory/non-inflammatory lesion counts, the differences in the temperatures of the DITI points on the face, sebum level, serum cortisol, DHEA-S, VAS, and IGA at baseline and at the end of the trial (at week 8) between the CBT treatment and placebo control groups. Safety tests (AST, ALT and creatinine) will be analyzed using the independent *T* test at screening and at the end of the trial (at week 8) between the CBT treatment and placebo control groups. A repeated measured analysis of covariance (ANCOVA) test will be used to examine the percentage change of inflammatory and non-inflammatory lesions, differences in the temperatures of the DITI points on the face, VAS, and IGA at weeks 0, 4, and 8 when controlling for baseline and other covariates. The correlation between inflammatory lesion count and the facial skin superficial temperature points at baseline, 4 weeks, and 8 weeks will be examined using the Pearson correlation test. Additionally, we will analyze the correlation between the temperatures of the DITI points and the severity of the KAGS using the Pearson correlation test. The change of KAGS from baseline to week 8 will be assessed using a Chi-square test or Fisher’s exact test. All adverse events reported during the study will be included in the case report forms; the incidence of adverse events will be calculated. The percentage of subjects with adverse events in each group will be calculated and compared using a Chi-square test or Fisher’s exact test. The evaluation of blinding success between the actual treatment and the perceived treatment allocations will be performed using a Chi-square test or Fisher’s exact test.

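### The declared outcome is the frequency of abnormal liver and kidney function, but the only analysis specified for AST, ALT and creatinine is a t test of values, which does not estimate that frequency and is insensitive to isolated large rises

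*Protocol article*

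**What the plan says.** All references are to the protocol article.

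- **Outcome.** Under Secondary outcomes, "the frequency of abnormal liver and kidney function during this trial will also be secondary outcomes". This is a count of participants.
- **Analysis.** Under Baseline data and outcome data, "Safety tests (AST, ALT and creatinine) will be analyzed using the independent" t test. The sentence continues: "test at screening and at the end of the trial (at week 8) between the CBT treatment and placebo control groups".
- **Categorical tests.** The same section uses chi-square or Fisher's exact tests for the KAGS change, for the blinding check and for adverse events ("The percentage of subjects with adverse events in each group will be calculated and compared using a Chi-square test or Fisher’s exact test"). It does not assign them to laboratory abnormality.
- **Timing.** Under Adverse events and safety monitoring, "Clinical laboratory tests, including AST / ALT and creatinine, will be performed at screening and week 8 (the end of the trial"). Table 2 shows the same two blood draws.
- **Population and missing data.** Under Statistical analysis plan, "Based on the ITT population, the primary outcome and safety outcome will be tested". That section also imputes missing values of drop-outs by LOCF and exempts no variable.
- **Display.** Also there, "Data will be displayed as the mean ± standard deviation (SD) for continuous data or n (%) for categorical data".
- **Limits.** The only numeric limits for these tests are the entry limits under Exclusion criteria: "aspartate transaminase (AST) ≥ 60 IU/L, alanine transaminase (ALT) ≥ 60 IU/L, and creatinine > 1.2 mg/dl". No definition of an on-treatment abnormality is given.

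**The concern.** The article is not silent on how the liver and kidney tests will be analysed. It names a method, and that method answers a different question from the declared outcome. A comparison of means asks whether the arms differ on average. The outcome asks how many participants had an abnormal result.

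The difference matters because laboratory harm may appear as a large rise in a few people. Such values move the arm mean only a little and also enlarge its standard deviation, so the t statistic stays small. The trial could report no significant difference in AST or ALT while one to three CBT participants have clear elevations. The article expects the results to bear on wider use of CBT, so a non-significant difference in means should not stand in for the frequency that was promised.

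**Working it through.** The plan states no figure on this point, so there is none to reproduce. The check has three parts.

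**1. Outcome against method.** Each method under Statistical methods was set against the declared frequency.

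| Method in the article | Applied to | Gives the frequency? |
|---|---|---|
| Independent t test | AST, ALT, creatinine values | No, compares means |
| Chi-square or Fisher's exact | KAGS change, adverse events, blinding | Not assigned to it |
| Display as n (%) | Categorical data in general | Could, but the outcome is not named |

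As worded, the t test compares the arms at each time point and does not use a participant's change from screening.

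**2. How the t test responds to isolated rises (illustration).** From the article: 28 per arm, two-sided 0.05. Assumed, not in the article: AST mean 25 and SD 8 IU/L in unaffected participants, k CBT participants between 90 and 150 IU/L (average 120), none on placebo.

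Mean difference = k × (120 − 25)/28, which is 3.4, 6.8 and 10.2 IU/L for k = 1, 2, 3.

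Taking all raised values at 120, the CBT variance is about [k(28 − k)/28 × 95² + (27 − k) × 64]/27:

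- k = 1: (8,703 + 1,664)/27 = 384, SD 19.6
- k = 2: (16,761 + 1,600)/27 = 680, SD 26.1
- k = 3: (24,174 + 1,536)/27 = 952, SD 30.9

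t = difference / √[(CBT variance + 64)/28]:

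- k = 1: 3.39/√(448/28) = 0.85
- k = 2: 6.79/√(744/28) = 1.32
- k = 3: 10.18/√(1,016/28) = 1.69

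The critical value on 54 degrees of freedom is 2.005, so all three fall short. Simulation gives the share of trials with p < 0.05. The last two columns use a different assumption: ALT mean 20, SD 8, raised values fixed at 80 or 150 IU/L.

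| k of 28 on CBT | AST 90–150 | ALT 80 | ALT 150 | Fisher p, k vs 0 |
|---|---|---|---|---|
| 1 | 2% | 4% | 0.4% | 1.00 |
| 2 | 5% | 8% | 2% | 0.49 |
| 3 | 18% | 19% | 16% | 0.24 |
| 4 | 49% | 42% | 60% | 0.11 |
| 5 | 83% | 68% | 95% | 0.051 |

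The insensitivity holds for one to three affected participants under each assumption. It fades from about four or five.

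Fisher's two-sided p for 5 versus 0 is 2 × C(28,5)/C(56,5) = 2 × 98,280/3,819,816 = 0.051.

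**3. What a count gives.** Exact (Clopper-Pearson) 95% intervals:

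- 3 of 28: 10.7%, interval 2.3% to 28.2%
- 0 of 28: upper limit 1 − 0.025^(1/28) = 12.3%
- 0 of 22, if 20% drop out (28 × 0.8 = 22.4): upper limit 1 − 0.025^(1/22) = 15.4%

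The denominator matters. Bloods are taken only at screening and week 8, so the only earlier value LOCF could carry forward is the screening value, which passed the entry limits. If LOCF is applied to laboratory data, every drop-out without a week-8 sample counts as normal.

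**The case against.** The strongest reply is that the gap is small. The frequency is a declared secondary outcome, the article says secondary outcomes will be analysed, and categorical data are to be shown as n (%). A count per arm is therefore within reach, and cut-offs and listings are commonly left to a fuller analysis plan. This stands in part: a reader might infer that the outcome will never be analysed, and the article does not support that. What remains is that the one analysis it does specify for these tests does not yield the outcome, and no section links the n (%) rule to it.

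The second reply is that Fisher's test would do no better. On significance that is correct: it cannot reach 0.05 at 1, 2 or 3 versus 0 of 28, where the t test occasionally does. The case for counts therefore cannot rest on power.

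Third, a reader might infer that widespread elevations would be hidden. They would not: at five affected participants the t test is significant in most simulated trials, and the required mean ± SD would show an inflated SD.

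Two further inferences are not supported. One is that a participant who enters with a stable, mildly raised value would be counted as an on-study abnormality. That needs a laboratory upper limit below 60 IU/L, which the article does not give. The other is that the screening comparison is misused as safety evidence. It can be read as an ordinary baseline comparison, and there is no need to remove it.

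**Conclusion.** The point holds in a limited form. The declared outcome is a per-participant frequency, and the only analysis specified for AST, ALT and creatinine is a t test of values, which does not estimate it. This follows from the article's own text and needs no assumption.

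The size of the insensitivity is illustrative. It rests on assumed AST or ALT distributions and applies to isolated large rises: roughly 2%, 5% and 18% of trials significant with 1, 2 or 3 of 28 affected. A trial of this size cannot establish a between-arm difference in such rare events by any test, so what is lost is visibility of individual cases and a stated bound on the rate. The change is worth making before the data are analysed, but it does not affect the primary efficacy analysis.

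**What to change.** Make the main laboratory safety analysis a count:

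- Per arm, give the number and percentage of participants whose week-8 AST, ALT or creatinine lies beyond a limit stated in advance, with exact 95% confidence intervals. The article's entry limits can serve as this threshold. Because they exclude at entry, each value beyond them is new since screening. This is a reporting definition only, not a rule for managing participants.
- Add a listing or shift table of screening and week-8 values.
- Use participants with an observed week-8 value as the denominator, state how many have none, and do not apply LOCF to laboratory values.
- Keep means, or change from screening, as supportive description. Label any Fisher's test as descriptive.

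The cost is wording in the protocol or analysis plan, with no new samples or visits. The downsides are wide intervals and a threshold that does not count rises staying below it. Those rises would appear only in the listing or shift table.

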### Outcome measures

#### Primary outcome

Primary outcome will be presented as the mean percentage change of inflammatory lesion counts from baseline to the end of the trial [8, 9].

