### Sample size

Calculation of the sample size for this trial was based on the effect size of the primary outcome, mean percent change of inflammatory acne lesion counts from baseline to week 8, reported in a previously published study [11]. The mean and standard deviation (SD) of the mean percent change of inflammatory acne lesion counts were -32.4 ± 44 and -15.1 ± 44.9 for the active treatment and control groups, respectively. To achieve 80 % power (β = 0.20), a significance level of 0.05 (α) in a two-tailed test, calculated using Cohen's d effect size values for t-tests (0.39), 28 participants, based on an estimated 20 % dropout rate, are needed for each group. This results in a required total of 56 for the trial. The mean and SD of the mean percent change of inflammatory acne lesion counts from this pilot study will be used for recalculation of the sample size for larger trials.

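### The repeated-measures ANCOVA, read literally, enters week 0 both as a response and as the baseline covariate, which shrinks any visit-averaged group estimate by one third

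*Protocol article*

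**What the plan says.** The Protocol article describes two analyses of overlapping outcomes under Baseline data and outcome data.

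- **Week-8 comparison.** "The independent *T* test will be used to examine the mean percentage change of the inflammatory/non-inflammatory lesion counts", and likewise DITI temperatures, VAS and IGA, between the arms at the end of the trial. This covers the primary outcome, which is defined thus: "Primary outcome will be presented as the mean percentage change of inflammatory lesion counts from baseline to the end of the trial".
- **Longitudinal analysis.** A repeated-measures ANCOVA "will be used to examine the percentage change of inflammatory and non-inflammatory lesions", together with DITI temperature differences, "VAS, and IGA at weeks 0, 4, and 8 when controlling for baseline and other covariates".

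Secondary outcomes fixes what week 0 is. The lesions "can be counted independently at weeks 0 (baseline), 4 and 8 (end of the trial"), and "VAS and IGA will be checked every session from baseline (just before randomization) through the 8 weeks after randomization". Week 0 is therefore the baseline, and for VAS and IGA it explicitly precedes randomization.

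The article does not say which quantity the repeated-measures model is to deliver: a group main effect, a group-by-time term or a contrast at one visit.

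**The concern.** A baseline-adjusted longitudinal model normally takes the post-treatment visits as responses and the baseline as covariate. Here the listed visits include the baseline itself.

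- For lesions, percentage change from baseline is 0 for every patient at week 0.
- For VAS and IGA, the week-0 response is the covariate.
- For DITI, one or the other applies, depending on whether temperature or change in temperature is analysed.

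Either way, the model contains a visit at which the arms cannot differ after adjustment and at which no residual variation remains. Equal residual variance over visits is then false.

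What is at stake is the size of a reported effect. An estimate averaged over the three visits includes a guaranteed zero. One of the variables is the primary outcome variable, so readers could be given a week-8 difference from the t test and a smaller figure from this model, with part of the gap being an artefact.

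**Working it through.** **Inputs**

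- Visits and covariate: weeks 0, 4 and 8, adjusted for baseline (Baseline data and outcome data); week 0 is the baseline (Secondary outcomes).
- Assumed week-8 percentage changes (Sample size): "were -32.4 ± 44 and -15.1 ± 44.9 for the active treatment and control groups, respectively".
- Week-4 effect: not given in the article. Assumed to be 0, half or all of the week-8 effect, to show a range.

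**Step 1. The plan's own figure.** Difference: 32.4 − 15.1 = 17.3 points. Pooled SD: √((44² + 44.9²)/2) = 44.45. Standardised effect: 17.3/44.45 = 0.389, which agrees with the stated 0.39. The article gives no figure for the repeated-measures model itself.

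**Step 2. The week-0 response.** Let Y0, Y4 and Y8 be the three values and G the arm. The adjusted group effect at visit t is the coefficient b_t of G when Y_t is regressed on G and Y0.

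- VAS or IGA at week 0: Y0 = 0 + 0·G + 1·Y0 fits perfectly, so b_0 = 0 and every residual is 0. Further covariates do not alter this.
- Percentage change at week 0: 100·(Y0 − Y0)/Y0 = 0 for everyone, so again b_0 = 0 with zero residuals.

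**Step 3. The visit average.** Least squares is linear in the response:

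- Weeks 0, 4, 8: (0 + b_4 + b_8)/3
- Weeks 4, 8: (b_4 + b_8)/2
- Ratio: 2/3, whatever b_4 and b_8 are.

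The residuals scale in the same way: (0 + e_4 + e_8)/3 is 2/3 of (e_4 + e_8)/2. The standard error and the interval width therefore also shrink to 2/3, and t = estimate/SE is unchanged.

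**Step 4. Size on the protocol's scale** (points of percentage change, 17.3 at week 8):

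| Assumed week-4 effect | Weeks 0, 4, 8 | Weeks 4, 8 |
|---|---|---|
| 0 | (0 + 0 + 17.3)/3 = 5.8 | (0 + 17.3)/2 = 8.65 |
| 8.65 | (0 + 8.65 + 17.3)/3 = 8.65 | (8.65 + 17.3)/2 = 13.0 |
| 17.3 | (0 + 17.3 + 17.3)/3 = 11.5 | (17.3 + 17.3)/2 = 17.3 |

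**Step 5. Simulation check.** 28 per arm, 4,000 runs, assumed correlation 0.5 between visits, and assumed effects of 0, 0.20 and 0.39 SD at weeks 0, 4 and 8:

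- Adjusted week-0 effect: zero to rounding error.
- Visit-averaged effect: 0.194 SD with week 0 and 0.290 SD without it, ratio 0.667.
- Week-8 effect alone: 0.385 SD.
- Largest difference between the two t statistics of the averaged effect: about 6 × 10⁻¹⁵. Power is 32.7% with and without week 0.
- Group-by-time test: rejected in 26.5% of runs with three visits and 10.6% with two. Dropping week 0 changes what that test asks.

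**The case against.** The strongest reply is that the damaged quantity is never promised. The article does not say that a visit-averaged group effect will be reported, and a week-8 contrast from the same model would carry no dilution. The sentence can also be read as listing the visits that supply data, with week 0 entering only as covariate. In a condensed article, the choice of reported term may sit in a fuller document.

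Much of this stands, and it limits the point to a conditional one. It does not remove it. The sentence puts week 0 beside weeks 4 and 8 as a time examined and also adjusts for baseline. If the looser reading is intended, the correction merely makes it explicit.

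A reader might infer more than the documents support:

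- **That week 0 halves the effect, from 17.3 to 8.65 points.** It does not. Under the half-size week-4 assumption, the fall from 17.3 to 13.0 comes from averaging in week 4. Week 0 accounts only for 13.0 to 8.65.
- **That power or the p-value suffers.** Estimate and standard error of the averaged effect shrink together, so neither changes. A separate simulation (6,000 trials) also put the type I error of the group-by-time test with week 0 included at 0.049 to 0.053.
- **That the primary result is compromised.** The week-8 comparison is a separate t test and does not use this model.
- **That the model cannot be fitted.** A mixed model with unstructured covariance would be singular, but the article does not propose one.

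**Conclusion.** The point holds as a moderate flaw in a supporting analysis. As written, week 0 is both response and covariate. Its adjusted group difference and residual variance are zero by construction, and nothing in the text directs the analyst to a contrast that avoids this.

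If the visit-averaged group effect is reported, the shrinkage to 2/3 in estimate and interval width is exact and needs no assumption beyond the literal reading. The figures in points rest on the protocol's planning difference at week 8 and on an assumed week-4 effect. The interval would be narrower only because it is centred on a smaller quantity. It would not be more informative about any post-treatment effect.

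**What to change.** Replace the sentence on the repeated-measures model with one that specifies:

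- responses at weeks 4 and 8 only;
- the week-0 value of the outcome as covariate only (for lesions, the baseline count);
- terms for treatment, visit and treatment-by-visit, alongside whatever other covariates are already intended;
- the adjusted treatment difference at week 8 as the reported estimate, with its 95% interval, and the week-4 difference beside it. A group effect averaged over visits should not be the headline result.

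The cost is one sentence. Data and software stay the same. There is one small downside: with two response visits, the treatment-by-visit test asks only whether the effect differs between weeks 4 and 8. It should not be used as the test of treatment effect. The change should be made before unblinding.

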**Methods/design:**

A randomized, double-blind, parallel-group, and placebo-controlled trial will be conducted. Fifty-six participants with acne vulgaris will be randomized into one of two groups: the CBT or placebo groups. After randomization, participants will be prescribed either CBT or placebo three times a day at a dose of 5 g after meals for 8 weeks. The following outcome measurements will be used in the examination of subjects: the mean percentage change and the count change of the inflammatory and non-inflammatory acne lesions, the temperature of facial points on digital infrared thermal imaging (DITI), serum cortisol, serum dehydroepiandrosterone-sulfate (DHEA-S), visual analogue scale (VAS), investigator global assessment (IGA), and severity score on the Korean Acne Grading System (KAGS) from baseline to the end of the trial.

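### Change in KAGS, an ordered severity grade, is compared between arms with a test that ignores order if there are three or more change categories; a rank or ordinal test would gain power at no cost

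*Protocol article*

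**What the plan says.** The statistical methods (Baseline data and outcome data) fix the between-group test for this outcome: "The change of KAGS from baseline to week 8 will be assessed using a Chi-square test", or else Fisher's exact test. No trend, rank or ordinal-model version is named.

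The article itself treats KAGS as ordered. The abstract lists "severity score on the Korean Acne Grading System (KAGS) from baseline to the end of the trial" among the outcome measurements. The sentence just before the chi-square sentence plans to analyse "the correlation between the temperatures of the DITI points and the severity of the KAGS using the Pearson correlation test", and a Pearson correlation uses both the order and the spacing of the grades.

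The article does not state how many KAGS grades there are, how change is grouped into categories, or any power for this outcome. Table 2 schedules KAGS at weeks 0, 4 and 8. The "Secondary outcomes" section names KAGS only for its correlation with facial temperature on thermal imaging, so change in KAGS ranks low among the outcomes.

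**The concern.** A Pearson chi-square test, or a Fisher test on a table with more than two columns, treats the columns as unordered labels. Suppose change in KAGS is tabulated as improved by two grades, improved by one, unchanged and worse. Permuting those labels leaves the p-value exactly as it was. The test then asks whether the two distributions differ in any way, whereas the trial asks whether acne becomes less severe on CBT.

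The cost is efficiency. With *k* categories the unordered test spreads its sensitivity over *k* − 1 degrees of freedom; a rank or trend test puts it on the single degree of freedom that describes a shift towards improvement. What is at stake is power on one secondary comparison in a trial of 56 participants. Validity is not at issue, and neither is the primary conclusion.

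**Working it through.** **Inputs from the article ("Sample size").** 28 per group, 1:1; 20% dropout, so 28 × 0.8 = 22.4, about 22 completers per group; "a significance level of 0.05 (α) in a two-tailed test"; mean percent change in inflammatory lesions −32.4 (SD 44) against −15.1 (SD 44.9).

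**Benchmark effect.** The article gives no effect size or power for KAGS, so there is no KAGS figure to reproduce. The only effect size it gives is for lesion counts. Pooled SD = √[(44² + 44.9²)/2] = 44.45, and 17.3/44.45 = 0.389, which agrees with the stated 0.39. It is borrowed here only as a benchmark; 0.8 SD is added as a large-effect case.

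**Assumptions.** Change categories are cut from a normal variable that is shifted by *d* SD on CBT. Assumed control-arm proportions:
- 3 categories: 0.30, 0.50, 0.20
- 4 categories: 0.15, 0.35, 0.35, 0.15
- 5 categories: 0.10, 0.25, 0.35, 0.20, 0.10
- 6 categories: 0.10, 0.20, 0.25, 0.25, 0.15, 0.05

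**Formulas.** Let *a* and *b* be the category proportions in the two arms and *m* = (*a* + *b*)/2.
- Unordered test: λ = *n* Σ (*a* − *b*)²/(2*m*), on *k* − 1 df.
- Rank test: with midranks *r* (cumulative *m* minus half of *m*), δ = Σ *r*(*b* − *a*) and *v* = Σ *m r*² − (Σ *m r*)², λ = *n*δ²/(2*v*), on 1 df.
- Power is the noncentral chi-square tail beyond the 5% critical value.

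**3 categories, d = 0.39, 28 per arm.** *b* = 0.180, 0.494, 0.326.
- Unordered: λ = 0.836 + 0.001 + 0.842 = 1.68; 2 df, critical value 5.99; power 0.195.
- Rank: δ = 0.0919, *v* = 0.0704, λ = 28 × 0.0919²/(2 × 0.0704) = 1.68; critical value 3.84; power 0.254.

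**5 categories, d = 0.39, 28 per arm.** *b* = 0.047, 0.172, 0.334, 0.260, 0.186.
- Unordered: λ = 0.528 + 0.406 + 0.010 + 0.221 + 0.729 = 1.89; 4 df, critical value 9.49; power 0.164.
- Rank: δ = 0.1017, *v* = 0.0779, λ = 28 × 0.1017²/(2 × 0.0779) = 1.86; power 0.276.

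The noncentrality is practically the same for both tests, so the loss comes from the extra degrees of freedom.

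**Power at 28 per arm, unordered against ordinal**

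| Categories | d = 0.39, formula | d = 0.39, exact tests | d = 0.8, formula |
|---|---|---|---|
| 3 | 0.195 vs 0.254 | 0.17 vs 0.22 | 0.62 vs 0.72 |
| 4 | 0.178 vs 0.268 | 0.16 vs 0.24 | 0.59 vs 0.75 |
| 5 | 0.164 vs 0.276 | 0.14 vs 0.28 | 0.56 vs 0.77 |
| 6 | 0.153 vs 0.281 | not run | 0.53 vs 0.78 |

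The exact column sets Fisher's test against an exact ordinal test, so the article's small-cell alternative has the same weakness.

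**Simulation of chi-square against rank-sum, 28 per arm**

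| Categories | d = 0.39 | d = 0.8 |
|---|---|---|
| 3 | 18% vs 23% (5 points) | 64% vs 75% (11 points) |
| 5 | 14% vs 28% (14 points) | 57% vs 79% (22 points) |

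With no effect, both tests rejected in about 4% to 6% of runs, so the gain is not bought with false positives.

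**Two categories.** If change is tabulated as improved or not, the two tests have practically the same power, about 0.20 each at d = 0.39. No order is lost, although collapsing has its own cost (0.20 against 0.31 for an uncollapsed continuous scale).

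**Sparse cells.** By the layouts above at 28 per arm, the smallest expected count is about 5.5 to 6.7 with 3 categories, 2.6 to 3.2 with 4, and 1.7 to 2.1 with 5.

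**The case against.** **The category layout is not stated.** This is the strongest objection. The permutation argument needs at least three change categories. With improved or not, a chi-square or Fisher test is standard. Category definitions are also a detail that an article may leave to the full protocol or SAP. This stands: it makes the point conditional and the size an assumption. But the article states no collapse, and it does fix a test that is inefficient for any finer table.

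**Sparseness is already covered.** A reader might infer that small cells make the planned test invalid. The article does not support that. The same sentence offers Fisher's exact test, type I error stays near 5%, and sparse cells are near certain only with about five categories; with three they depend on how evenly the categories fill.

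**Test choice is not what would hide a benefit.** A reader might also infer that a real KAGS benefit would be missed because of the chi-square test. At d = 0.39 an ordinal test has only about 23% to 28% power with 28 per arm, so it too would miss the effect in roughly three trials out of four. Sample size dominates, and that is a separate matter on which this point does not depend.

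**Use of KAGS in a Pearson correlation is not a contradiction.** Correlating the severity level and tabulating its change are different analyses and may use different summaries. The correlation shows that the article regards KAGS as ordered, and no more is claimed from it here.

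**The outcome ranks low.** This stands. Lesion count is primary, and another ordered global scale, the IGA, is already compared by methods that use its order (t test and repeated-measures ANCOVA).

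**Conclusion.** The point holds as an efficiency point. For an ordered severity grade, the article fixes a between-group test that ignores order whenever change has three or more categories, and the Fisher alternative does not repair this.

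By simulation at 28 per arm, the loss at the borrowed benchmark of 0.39 SD is about 5 percentage points with 3 categories and 14 with 5. At 0.8 SD it is about 11 and 22 points. It is nil for a two-category table. These figures rest on an assumed latent-normal shift and assumed category layouts, because the article gives neither the number of grades nor how change is grouped. The direction does not depend on the layout: the ordinal test was the more powerful in every layout of three or more categories tried.

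The consequence is limited to a minor secondary outcome. No primary conclusion depends on it, and the change does not make the KAGS comparison well powered.

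**What to change.** Replace the chi-square or Fisher test for change in KAGS with one of the following, chosen before unblinding:
- a Wilcoxon rank-sum test (or a linear-by-linear trend test) on the change in grade between arms; use the exact version if the table is sparse; or
- a proportional-odds model of the week-8 grade with treatment and baseline grade as terms.

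Keep the table of change categories by arm as description only, and state how change is categorised. A stratified rank test (van Elteren) cannot be specified from the article as it stands: the randomisation is called stratified, but no stratification factor is named.

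The cost is one sentence of analysis wording, with no new data and no extra participants.
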